**Sample size estimation**

This study is a randomized controlled trial. The experimental group will be received extracorporeal cardiac shock wave therapy intervention, while the control group will be received conventional treatment for acute myocardial infarction. The left ventricular ejection fraction (LVEF) of the study object is one of the observed outcome indicators. According to the literature review results, the average LVEF in the control group is 58.0 ± 11.7 points. It is estimated that LVEF in the shock wave intervention group can be increased by 8.1%,α= 0.05, and the assurance is 90%. Calculate the sample size according to the following sample size calculation formula

[figure not shown]

44 cases can be calculated, considering 1:1 randomization, that is, 44 cases in the intervention group and 44 cases in the control group, and considering 15% will lost to follow-up and refuse to visit, finally, at least 51 subjects in the intervention group and 51 subjects in the control group will be needed, and a total of at least 102 subjects will be included.

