**Methodology**

**Study aim and objectives**

This study is order to provide a new therapeutic method for patients with myocardial ischemia-reperfusion injury and reveal the possible mechanism of ECSW for ischemia-reperfusion injury.

The objectives of the study as follows:

**I.** The primary endpoint of this study is 2-year all-cause death, rehospitalization due to cardiovascular disease, major adverse cardiovascular and cerebrovascular events, including cardiac death, myocardial infarction, heart failure, arrhythmia, emergency coronary revascularization, and stroke;

**II.**Secondary endpoints are improvement in angina, quality of life, cardiac structure and function, coronary microcirculation, and expression level of endothelial progenitor cell-derived miR-140-3p.

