**Research hypothesis**

We hypothesized that extracorporeal cardiac shock therapy would also be effective in reducing clinical endpoints in patients with STEMI reperfusion.

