
**Data collection and follow-up**

All necessary data will be collected and recorded in electronic case report forms for this study, which will be mainly obtained from medical records(such as electronic or paper medical records), local laboratory testing records and investigator’s evaluation on patients. Relevant baseline data will be collected at the time of enrollment in patients with acute ST-segment elevation myocardial infarction reperfusion, mainly including:demography(age, gender, race), medical history, signs, treatment, biochemical values(mainly including serum electrolyte value, serum AST, serum ALT, serum creatinine, serum BUN, serum CK-mb, cTNI, BNP and HsCRP), imaging examination indicators(Echocardiography will be used to measure left ventricular ejection fraction (LVEF), left ventricular end diastolic diameter(LVEDD), global longitudinal strain, myocardial stress changes in each segment and synchrony of myocardial motion, left ventricular contrast echocardiography will assess coronary microcirculation), relevant scale scores(mainly will include 6-minute walk test, Canada Cardiovascular Society (CCS) angina classification, Seattle angina scale (SAQ) score, quality of life scale (SF-8)) (Appendix D) and expression level of miR-140-3p in endothelial progenitor cell (EPCs)-derived exosomes in peripheral blood;Biochemical values, imaging parameters, scores of relevant scales, expression level of miR-140-3p in endothelial progenitor cell (EPCs)-derived exosomes and major adverse cardiovascular events (which will include all-cause death, readmission due to cardiovascular disease, cardiac death, myocardial infarction, heart failure, arrhythmia, emergency coronary revascularization and stroke) will be collected in the test group and control group at 1, 4, 6, 12 and 24 months.

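### The 44 per arm and 90% power are for LVEF, a secondary outcome; the primary 2-year clinical composite has no stated event rate, effect or power, and 102 patients do not power it for a moderate effect

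*Protocol*

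**What the plan says.** Under Study aim and objectives, the Protocol states: "The primary endpoint of this study is 2-year all-cause death, rehospitalization due to cardiovascular disease, major adverse cardiovascular and cerebrovascular events". The listed components include cardiac death, myocardial infarction, heart failure, arrhythmia, emergency revascularization and stroke. The Research hypothesis section matches this, expecting that "extracorporeal cardiac shock therapy would also be effective in reducing clinical endpoints in patients with STEMI reperfusion".

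The same objectives section continues: "Secondary endpoints are improvement in angina, quality of life, cardiac structure and function, coronary microcirculation". LVEF is not named there. Data collection and follow-up lists it among the echocardiographic measurements, so it belongs under cardiac structure and function.

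Sample size estimation uses only LVEF, introduced with "The left ventricular ejection fraction (LVEF) of the study object is one of the observed outcome indicators". Its inputs are "the average LVEF in the control group is 58.0 ± 11.7 points", then "It is estimated that LVEF in the shock wave intervention group can be increased by 8.1" percent, then "α= 0.05, and the assurance is 90" percent. The result is 44 per arm, raised to 51 per arm (102 in total) for 15% loss. The Protocol gives no event rate, hazard ratio, event count or power for the composite.

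**The concern.** The only power figure in the Protocol belongs to an outcome that the Protocol does not make primary. The test that answers the stated hypothesis, a comparison of 2-year clinical events, has no sample size justification.

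If the therapy has a moderate benefit on events, a trial of this size would more often than not return a non-significant primary result. Without a statement of what the trial can detect on events, that result is easy to misinterpret, because the one figure available to a reader is 90%. Participants also commit to 24 months of follow-up for a primary question whose expected precision the plan does not state.

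**Working it through.** **1. The plan's own figure.** Inputs from Sample size estimation: difference 8.1, SD 11.7, α 0.05 (taken as two-sided, since sidedness is not stated), power 90%.

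n per arm = 2(1.960 + 1.282)² / (8.1/11.7)² = 43.85, so 44. This matches the plan. One-sided testing would give 36, so the plan's figure is two-sided. Then 44 × 1.15 = 50.6, so 51 per arm and 102 in total, as stated. (Dividing by 0.85 gives 52, a trivial difference.)

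The match holds only if 8.1% means absolute LVEF points. Read as relative to 58.0, the difference is 0.081 × 58.0 = 4.7 points. That needs 131 per arm, and 44 per arm gives about 47% power.

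**2. A bound on the composite that needs no event rate.** Data analysis plans Kaplan-Meier, log-rank and Cox methods for time-to-event variables. With 1:1 allocation and two-sided 0.05, the Schoenfeld formula gives the events needed for 90% power:

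D = 4(1.960 + 1.282)² / (ln HR)² = 4 × 10.507 / (ln HR)²

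| True HR | Events needed | Compared with the trial |
|---|---|---|
| 0.7 | 42.03 / 0.1272 = 330.4, so 331 | more than the 102 enrolled |
| 0.6 | 42.03 / 0.2609 = 161.1, so 162 | more than the 102 enrolled |
| 0.5 | 42.03 / 0.4805 = 87.5, so 88 | equal to all 88 evaluable patients |

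A patient contributes at most one first event. No event rate can therefore supply the events needed for HR 0.7 or 0.6.

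**3. Power under assumed rates.** The documents give no composite rate, so control 2-year rates (pc) of 20% to 60% are assumed. All 51 per arm are counted, which favours the trial. Formulas:

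- pt = 1 − (1 − pc)^HR
- D = 51 × (pc + pt)
- power = Φ(|ln HR| × √D / 2 − 1.96)

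| Control rate | HR 0.7: events, power | HR 0.5: events, power | True HR for 90% power |
|---|---|---|---|
| 20% | 17.6, 11% | 15.6, 28% | 0.15 |
| 30% | 26.6, 15% | 23.6, 39% | 0.23 |
| 40% | 35.7, 19% | 31.9, 50% | 0.29 |
| 50% | 45.1, 22% | 40.4, 60% | 0.34 |
| 60% | 54.7, 26% | 49.3, 68% | 0.38 |

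The last column solves for HR with the event count falling as the effect grows. At a 40% rate, for example, HR 0.29 gives 27.4 events and 90% power. With 44 per arm instead of 51, power at HR 0.7 and a 30% rate is 13% rather than 15%, so the choice matters little.

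**The case against.** **The composite is broad.** It counts any cardiovascular rehospitalization and any arrhythmia, and eligibility requires CCS grade II or above with reversible ischaemia. The event rate could be high, and every power figure in step 3 rests on an assumed rate. This stands, and it is why the range runs to 60%. A reader might infer that 102 patients cannot test the composite at all, or that a null result would be uninformative. The documents do not support that. A very large effect at a high rate could be detected, and a null result with a confidence interval is imprecise rather than empty. The step 2 bound for moderate effects does not depend on the rate.

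**Significance is not power.** A reader might infer that a significant primary result would need an implausibly large effect. With 25 to 30 events, p < 0.05 needs an observed hazard ratio of about exp(−2 × 1.96/√D) = 0.46 to 0.49. That is less extreme than the true hazard ratio needed for 90% power at comparable event counts, and nothing in the Protocol sets a limit on plausible effects.

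**The 90% is openly tied to LVEF.** This is true: the section never claims it for the composite. It would be speculation to say that the trial will be read as a negative trial with 90% power. The gap remains, because the primary endpoint has no figure of its own.

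**A statistical analysis plan may cover it.** The sample size rationale is in the Protocol, and it powers an outcome that the same Protocol makes secondary. That mismatch stands in the present text.

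**Conclusion.** The mismatch holds and should be corrected. The stated 44 per arm and 90% reproduce for LVEF (read in absolute points) and do not apply to the primary composite. The trial is not powered for a moderate effect on that composite: whatever the event rate, the events required at hazard ratios of 0.7 and 0.6 exceed the number of patients.

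Under assumed control rates of 20-60% with 51 per arm, power is about 11-26% at HR 0.7 and 28-68% at HR 0.5, and 90% power needs a true HR of about 0.15-0.38. These ranges rest on the assumed rates, two-sided 0.05, proportional hazards and the Schoenfeld approximation, which is rough at small event counts. LVEF's secondary status is inferred from its being a measure of cardiac function, since the endpoint list does not name it.

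**What to change.** In Sample size estimation:

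- State that the 44 per arm and 90% power are for LVEF only, and that 8.1% means absolute points.
- For the composite, give the assumed range of control 2-year rates, the approximate power and the detectable hazard ratio.
- State that the composite will be reported as a hazard ratio with 95% CI, and that a non-significant result will not be read as no effect.

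An alternative for the sponsor to weigh is to make LVEF at one named visit primary and the composite secondary. The sample size would then fit the primary endpoint, provided that the absolute reading of 8.1% is the intended one. This changes the registered primary endpoint and moves the claim from clinical events to a surrogate, so it is a real trade-off and not a wording change.

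The first option costs a protocol amendment and no extra patients. Its downside is that the stated power for the primary endpoint becomes visibly low.

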**Data analysis**

Statistical analysis will be performed using SPSS 26.0, Graphpad Prism Software, and for quantitative data, the results will be presented as mean ± standard deviation (x ± s) or median (m) and interquartile range (IQR), between-group comparisons will use Welch's t-test or Wilcoxon's rank-sum test; categorical data will be presented as frequencies or percentages, and between-group comparisons will use the chi-square test or Fisher's exact probability method, time-to-event variables will be estimated using the Kaplan-Meier method, compared using the log-rank or generalized rank-sum test methods, and Cox regression models will be established, with P values less than 0.05 considered statistically significant.

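### The 15% loss allowance is multiplied on instead of divided out, so the stated minimum of 51 per arm falls just short of the 44 evaluable patients required (minor)

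*Protocol*

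**What the plan says.** The protocol's section on sample size estimation sizes the trial on LVEF, described there this way: "The left ventricular ejection fraction (LVEF) of the study object is one of the observed outcome indicators". The control value is taken from the literature: "the average LVEF in the control group is 58.0 ± 11.7 points". For the effect, the section says "LVEF in the shock wave intervention group can be increased by 8.1" percent. Alpha is 0.05 and "the assurance is 90" percent, which is the power. The formula is a figure that is not shown in the copy at hand.

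The result is 44 evaluable patients per arm: "considering 1:1 randomization, that is, 44 cases in the intervention group and 44 cases in the control group". The section then expects 15% of patients to be lost or to decline visits and concludes that "finally, at least 51 subjects in the intervention group and 51 subjects in the control group will be needed", a minimum of 102 in total.

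**The concern.** The last step does not follow from the ones before it. A 15% loss is a share of the patients enrolled, so the number to enrol is the number needed divided by 0.85. The stated 51 is what results from adding 15% of 44 to 44. If losses run at the rate the protocol itself assumes, a trial that stops at its stated minimum should expect to fall below its own requirement.

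What is at stake is the accuracy of the sample size statement and a small part of the power claimed for LVEF.

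**Working it through.** **Inputs**, all from the protocol's sample size section: control mean 58.0, SD 11.7, increase 8.1, alpha 0.05, power 90%, allocation 1:1, loss 15%. The text does not state whether alpha is one- or two-sided, or whether the 8.1% is absolute or relative.

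**Step 1: reproduce the 44.** Normal approximation for two means, two-sided alpha, difference of 8.1 points:

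n per arm = 2 x (1.960 + 1.282)² x (11.7/8.1)² = 43.85, rounded up to 44.

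This matches the protocol exactly. The other readings do not:

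| Reading of the 8.1% | Alpha | n per arm |
|---|---|---|
| Absolute, 8.1 points | two-sided | 43.85, so **44** |
| Absolute, 8.1 points | one-sided | 35.7, so 36 |
| Relative, 0.081 x 58.0 = 4.70 points | two-sided | 130.3, so 131 |
| Relative, 4.70 points | one-sided | 106.2, so 107 |

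The protocol's own figure therefore identifies the intended reading: 58.0 against 66.1, two-sided.

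**Step 2: reproduce the 51.** 44 x 1.15 = 50.6, rounded up to 51. This matches.

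**Step 3: apply the loss to those enrolled.** 44/(1 - 0.15) = 51.76, rounded up to 52 per arm, or 104 in total.

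**Step 4: expected evaluable patients.**

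- 51 per arm: 51 x 0.85 = 43.35, which is 0.65 below 44.
- 52 per arm: 52 x 0.85 = 44.2, which meets 44.
- Largest loss that 51 per arm can absorb: 1 - 44/51 = 7/51 = 13.7%.

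**Step 5: power at the expected numbers.** Same approximation, power = Φ(8.1/(11.7 x √(2/n)) - 1.960):

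- n = 44: Φ(3.247 - 1.960) = Φ(1.287) = 90.1%.
- n = 43.35: Φ(3.223 - 1.960) = Φ(1.263) = 89.7%.

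The loss of power due to this step is about 0.4 percentage points.

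**The case against.** The strongest reply is that the slip does not matter. It concerns less than one patient per arm, and the correction adds one per arm, about 2% of the total. The protocol also allocates by coin toss: with 102 patients the SD of an arm's size is √(102 x 0.25) = 5.05, far more than the correction. Finally, LVEF is not the primary endpoint, which the objectives section gives as a set of clinical events over two years. All of this stands, and it is why the point is minor.

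It can also be said that 51 and 102 are only minimums, so enrolling 52 or 53 per arm would comply. That does not rescue the figure. A minimum is the number that has to be sufficient, and stopping at exactly 102 would follow the protocol and still miss 44 per arm in expectation.

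Two stronger readings are tempting, and the documents support neither.

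- **Relative effect.** A reader might take the 8.1% as relative to 58.0, because the control value is given in points and the effect in percent, and conclude that the trial is far too small. LVEF is itself measured in percent, however, and the relative reading leads to 131 per arm, not to the protocol's 44. The wording is loose, but the arithmetic settles it.
- **t-test basis.** The data analysis section says "between-group comparisons will use Welch's t-test or Wilcoxon's rank-sum test", and a t-based formula gives 45 where the normal approximation gives 44. A reader might call the 44 wrong as well. The normal approximation is a standard formula, the data analysis wording is a general statement for quantitative data and does not fix the basis for sizing, and the formula used is not visible. This is a choice of formula and not an error.

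**Conclusion.** The point holds as a minor correction: the stated minimum of 51 per arm (102 in total) is wrong as written on the protocol's own inputs. Dividing by 0.85 gives 52 per arm and 104 in total. The expected shortfall is 0.65 evaluable patients per arm, and power for LVEF is about 89.7% rather than 90.1%.

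This assumes that the 15% is a share of those enrolled, that losses are equal in the two arms, and that the 44 comes from the two-sided normal approximation with an absolute difference of 8.1 points, which reproduces it exactly.

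A reader might infer that the imprecise effect wording contributes to the shortfall. It does not: the loss step takes 44 as given. A reader might also infer that the trial's primary conclusion is weakened. The calculation concerns LVEF only, so nothing about power for the clinical events follows from this slip.

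**What to change.** Correct the final step of the sample size section in one of these ways:

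- Keep 51 per arm (102 in total) and state that this allows for 13.7% loss.
- Keep 102 and state that it gives about 89.7% power for LVEF at 15% loss (normal approximation).
- Change the stated minimum to 52 per arm, 104 in total.

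In the same sentence, state the effect as a difference of 8.1 percentage points in LVEF (58.0 against 66.1, SD 11.7) with two-sided alpha 0.05. This only makes explicit the reading that already gives 44.

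The cost is a sentence of text. The first two options add no patients, and the third adds two to the stated minimum.

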**Study intervention**

The experimental group will be given extracorporeal cardiac shock wave therapy 2 - 3 days after PCI for acute myocardial infarction, and the treatment course is 3 months. 9 treatments were completed within 3 months as 1 treatment course, 1 week per month, 3 weeks rest, and 3 times of extracorporeal cardiac shock wave will be performed in each treatment week, respectively on the 1st, 3rd, and 5th days of the treatment week, lasting for 3 months in total; The control group received conventional treatment for acute myocardial infarction.

The experimental group meeting the inclusion and exclusion criteria will be treated by the external cardiac shock therapy instrument in accordance with standard operating procedures, specifically to determine the treatment target myocardium: according to the conventional left ventricular myocardium will be divided into 17 segments, through load ultrasound or load nuclide myocardial perfusion imaging, combined with ECG, coronary angiography and other results, to determine the therapeutic bullsey-eye muscle segments. Vital signs monitoring: During treatment, patients will be required to lie in a quiet position, and 12-lead combined electrocardiogram (ECG) will be recorded, connected to ECG, blood pressure and oxygen saturation monitoring. Setting the height of the water sac: Adjust the height of the water sac (positioning) according to the location of the target myocardium before positioning, and then move the ultrasonic probe down and slightly protruding from the surface of the water sac to achieve clear positioning. After positioning, it is appropriate to increase the height of the water sac until the patient's chest wall is lightly touched but not compressed, in order to reduce the energy attenuation in the process of seismic wave conduction. Airborne ultrasonic detection of bull's eye muscle segments: When the probe moves down and touches the chest wall, the left ventricular long axis image will be displayed first, and then the ultrasonic adjustment button will be rotated clockwise to display the left ventricular short axis, four chambers and two chambers of the left heart section in turn. When more than two sections lock the same segment together, the positioning will be regarded as successful. Energy control: Raise the probe after positioning so as not to interfere with shock wave release. Then press the shock wave releaser, starting from a small energy level of 0.8 (equivalent to 0.024 mJ/mm2). The successful release is marked by the occurrence of "Da, da" sound consistent with the patient's heart rate. Every 200 points is one frequency cycle. If there is no special, the energy level can be gradually adjusted to level 3 (0.09 mJ/mm2); Fine-tuning of treatment points in the target area: under normal circumstances, we will line a combination of 9 points between 1 ~ 0 ~ -1 or 2 ~ 0 ~ -2 for each area, and issue 200 pulses at each point, giving a total of 1800 pulses (9×200). Monitoring during treatment: ask patients about their symptoms and observe their vital signs and electrocardiogram. In case of discomfort or changes in electrocardiogram, lower the energy level first and continue to observe, treat as appropriate, record and analyze the causes in detail.

**Data collection and follow-up**

All necessary data will be collected and recorded in electronic case report forms for this study, which will be mainly obtained from medical records(such as electronic or paper medical records), local laboratory testing records and investigator’s evaluation on patients. Relevant baseline data will be collected at the time of enrollment in patients with acute ST-segment elevation myocardial infarction reperfusion, mainly including:demography(age, gender, race), medical history, signs, treatment, biochemical values(mainly including serum electrolyte value, serum AST, serum ALT, serum creatinine, serum BUN, serum CK-mb, cTNI, BNP and HsCRP), imaging examination indicators(Echocardiography will be used to measure left ventricular ejection fraction (LVEF), left ventricular end diastolic diameter(LVEDD), global longitudinal strain, myocardial stress changes in each segment and synchrony of myocardial motion, left ventricular contrast echocardiography will assess coronary microcirculation), relevant scale scores(mainly will include 6-minute walk test, Canada Cardiovascular Society (CCS) angina classification, Seattle angina scale (SAQ) score, quality of life scale (SF-8)) (Appendix D) and expression level of miR-140-3p in endothelial progenitor cell (EPCs)-derived exosomes in peripheral blood;Biochemical values, imaging parameters, scores of relevant scales, expression level of miR-140-3p in endothelial progenitor cell (EPCs)-derived exosomes and major adverse cardiovascular events (which will include all-cause death, readmission due to cardiovascular disease, cardiac death, myocardial infarction, heart failure, arrhythmia, emergency coronary revascularization and stroke) will be collected in the test group and control group at 1, 4, 6, 12 and 24 months.

